## **3.2. Methodology**

### **3.2.1. Approach**

The framework for analyzing the program’s impact will be experimental: all villages in the study area (*n*=162) will be randomly assigned either to an intervention group or a control group. Over a period of 24 months, cross-sectional surveys of children aged six to 29 months and their mothers will be conducted in these villages; one survey will take place before the program begins (hereinafter referred to as “baseline”) and the second will be conducted at the program’s end (hereinafter referred to as “endline”). A difference-in-differences analysis will permit both to determine whether situational evolution between the baseline survey and the endline survey differs significantly between the intervention group and the control group, and to conclude what impact is attributable to cash transfers and/or the flexible conditions with which they are associated.

Rationale for selected impact evaluation design:

1. ***Repeated cross-sectional vs. longitudinal design*.** We propose to use a repeated cross-sectional survey design rather than a longitudinal design primarily because our previous experience has shown that usual delays in program roll-out and full implementation can have profound effects on the evaluation study cohort (e.g. children aging out of the “window of opportunity” for maximum nutritional impact of the intervention – see point 2 below), making the cohort unusable for assessing impact on age-sensitive outcomes such as child feeding practices or stunting. Additional constraints of longitudinal designs include the logistical complexity and related additional cost of tracking individual children over time, compared to sampling children of a given age in a repeated cross-sectional design. However, given that our team has extensive experience with both types of designs, we are open to discussions with UNICEF and the World Bank regarding alternative designs.

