### **3.2.6. Data analysis**

Statistical analyses will be performed using either R or STATA software. These analyses will take into account the characteristics of the sampling plan in strata (prefectures) and clusters (villages), and will be weighted according to village population sizes. The *p*-value, alpha, will be set at 0.05 and used as the threshold of significance for all comparisons.

Before the actual impact analysis, the results regarding indicators of interest will be presented by randomization group (intervention/beneficiary and control/non-beneficiary) at baseline in a descriptive fashion and by randomization group and prefecture at endline. Results concerning quantitative variables will be expressed in arithmetic mean values, while those dealing with qualitative variables will be expressed as frequencies (in percentages).

In order to evaluate program impact on the indicators of interest, the difference-in-differences method will be used. This method consists of comparing the intervention group to the control group both before and after the introduction of cash transfers. The underlying hypothesis is that absent the cash transfer program, the mean evolution of the indicators of interest should be the same in both groups. By considering an interaction term between the phase (baseline or endline) and the randomization group (intervention or control), this method permits evaluating whether the indicators’ evolution between the baseline and endline surveys differs significantly between the two groups. In other words, the difference-in-differences estimator compares the difference observed in the intervention group before and after program implementation with that observed in the control group. It also enables taking pre-existing differences between the intervention and control groups into account, as well as temporal effects, and thus allows for a conclusion on the existence of an impact attributable to cash transfers and/or the flexible conditionalities associated with them.

To this end, quantitative variable analysis will be conducted with the help of linear regression models, while qualitative binary variable analysis will be conducted with the help of logistic regression models. We will formulate
[figure not shown]

[figure not shown]
 (the estimation of the indicator of interest) and
[figure not shown]

[figure not shown]

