 depending on whether we are interested in, respectively, a quantitative variable or a qualitative binary variable, in the following form:

**
[figure not shown]
=
[figure not shown]
+
[figure not shown]
*phase+
[figure not shown]
*group+
[figure not shown]
*phase*group**

Here, “phase” represents the survey (coded 0 for baseline and 1 for endline) and “group” represents the randomization group (coded 0 for the control group and 1 for the intervention group).
[figure not shown]
 is the effect of the phase (the difference between baseline and endline surveys),
[figure not shown]
 represents the difference between individuals in the intervention group and the control group, and
[figure not shown]
 represents the intervention’s effect on the intervention group or the difference-in-differences estimator.

**Using birthweight as an example, the table and figure below illustrate the significance of the various coefficients described above:**

[figure not shown]

[figure not shown]

Initially, analyses will be carried out via intention-to-treat (ITT) analysis; mother-child pairs (“CME”) and households will be analyzed within their initial randomization group, whether or not they have actually received cash transfers. A later set of analyses will use per-protocol analysis (or treatment-on-the-treated [TOT]); only mother-child pairs who have actually received cash transfers will remain in the intervention group, and those pairs who have not will be excluded from further analyses.

Pre-specified outcomes to be analyzed are as follows:

Primary outcomes:

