-Expected benefits: these primarily concern participating mothers and children, as cash transfers will hopefully better their everyday lives (through improved nutritional intake, better medical monitoring, etc.) and lead to a reduction in morbidity and an enhanced nutritional status. The benefits will also concern other children in the household via flexible conditionalities (schooling of eligible children’s siblings, avoiding foster care); additionally, these children should profit from their mothers’ knowledge of nutrition, health, and child welfare, accrued through monthly sensitization sessions. The entire household could potentially benefit from the fact that the cash may be freely spent; notably, household food security is expected to improve. Finally, benefits will also pertain to the entire local community, as the study should lead to improvements in the interventions themselves or those of the same type; in a broader sense, the study will allow national and international decision-makers to be better informed about the potential effects, whether beneficial or detrimental, of this program.

-Comparison group: program effects will be evaluated through a comparison with a group of women (and their children) who will not receive cash transfers, but who nonetheless will benefit from UNICEF activities comprising detection and treatment of severe acute malnutrition.

-Emergencies: all participants, whether from the beneficiary group or the control group, are eligible for medical treatment in the event of emergencies observed during visits; medical costs will be covered in cases of severe health problems, as treatment of malnutrition is already provided for as part of the ICCM-Nut.

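### The analysis labelled treatment-on-the-treated drops unpaid pairs from the intervention group only, with no phase limit, so it does not estimate that effect and mixes programme effect with selection

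*Protocol*

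**What the plan says.** Protocol section 3.2.6 sets the order of the analyses. Intention-to-treat comes first: "Initially, analyses will be carried out via intention-to-treat (ITT) analysis". Pairs and households stay in the group to which their village was randomised, paid or not. Then: "A later set of analyses will use per-protocol analysis (or treatment-on-the-treated [TOT"]). The rule for that second analysis is that "only mother-child pairs who have actually received cash transfers will remain in the intervention group, and those pairs who have not will be excluded". No restriction is set for controls, and no survey phase is named.

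The only impact model in the section is the difference-in-differences regression on phase, group and their product, where phase "represents the survey (coded 0 for baseline and 1 for endline") and the product term carries the programme effect.

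Three facts from elsewhere in the Protocol bear on the rule:

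- Section 3.2.1, on the baseline: "one survey will take place before the program begins".
- Section 3.2.1, on the design: "We propose to use a repeated cross-sectional survey design rather than a longitudinal design". Baseline and endline pairs are therefore separate samples, and no link from baseline pairs to later payment is described.
- Section IV, on the comparison group: it is "a group of women (and their children) who will not receive cash transfers".

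**The concern.** Per-protocol and TOT are treated as one analysis, but they are different quantities. A TOT effect is the effect of receiving cash among those who receive it. To estimate it from a randomised comparison, everyone must stay as randomised, and assignment is used to correct for incomplete receipt. The stated rule instead removes a subset of one arm, chosen by something that happens after randomisation. The families in control villages who would not have been paid stay in the control mean, because receipt cannot be observed where no cash is offered.

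The rule also fits badly into a difference-in-differences model with a pre-programme baseline, since no baseline pair can meet the receipt criterion.

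What is at stake is a secondary result that readers would take as the effect of actually receiving the money, when part of it may only be a difference between families who were paid and families who were not.

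**Working it through.** The plan gives no figure for this analysis, so there is nothing to reproduce. The check has four steps.

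**Inputs from the Protocol.** Four design cells (phase 0/1 by group 0/1) and the receipt rule, section 3.2.6. Baseline before the programme, section 3.2.1. Controls unpaid, section IV. 81 villages per group and a target HAZ difference of 0.20, section 3.2.3.

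**Assumed inputs, not in the Protocol.** c, the share of intervention pairs paid by endline. D, the mean HAZ of recipients minus that of non-recipients for reasons other than cash. For the simulation: 11 children per village and survey, SD 1, intra-village correlation 0.05.

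**Step 1: literal reading.** With all four cells, the design matrix [1, phase, group, phase×group] has rank 4 of 4. If unpaid pairs are dropped at both surveys, the baseline intervention cell is empty and the rank falls to 3 of 4. In the cells that remain, group and phase×group always take the same value, so only their sum is identified. That sum is the endline contrast of paid pairs with all controls, and no difference-in-differences estimate exists.

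**Step 2: endline-only reading.** All four cells are filled. With no programme effect, the endline intervention mean is c·μ_R + (1−c)·μ_N for everyone and μ_R for recipients only. The rule therefore shifts that one cell by

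μ_R − [c·μ_R + (1−c)·μ_N] = (1−c)(μ_R − μ_N) = (1−c)·D.

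The other three cells are unchanged, so the whole shift passes into the interaction. Its size in z, for positive D (a negative D reverses the sign):

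| c | D=0.1 | D=0.2 | D=0.3 | D=0.4 | D=0.5 |
|---|---|---|---|---|---|
| 0.95 | 0.005 | 0.010 | 0.015 | 0.020 | 0.025 |
| 0.90 | 0.010 | 0.020 | 0.030 | 0.040 | 0.050 |
| 0.80 | 0.020 | 0.040 | 0.060 | 0.080 | 0.100 |
| 0.70 | 0.030 | 0.060 | 0.090 | 0.120 | 0.150 |

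Relative to 0.20, the 95% row runs from 0.005/0.20 = 2.5% to 0.025/0.20 = 12.5%. Coverage of 80–90% with D of 0.2–0.4 runs from 0.02/0.20 = 10% to 0.08/0.20 = 40%.

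**Step 3: simulation with no true effect** (2,000 runs, village-level differences, nominal 5% test):

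| c, D | Formula | Exclusion rule: bias | Exclusion rule: false positives | ITT: bias | ITT: false positives |
|---|---|---|---|---|---|
| 0.90, 0.3 | 0.03 | 0.028 | 6.6% | −0.002 | 4.5% |
| 0.80, 0.3 | 0.06 | 0.059 | 13.6% | −0.001 | 5.0% |
| 0.70, 0.5 | 0.15 | 0.147 | 54.7% | −0.003 | 5.8% |

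The simulation agrees with the formula, and intention-to-treat stays unbiased.

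**Step 4: what a TOT estimator would give.** Suppose cash adds τ to HAZ for those paid and assignment does nothing to those not paid. Intention-to-treat then estimates c·τ, and dividing by c returns τ. The exclusion rule applied at endline estimates τ + (1−c)·D. The two agree only if everyone is paid or D is zero.

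**The case against.** Four points can be made for the plan.

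*Intention-to-treat comes first.* This stands. The conclusion on HAZ, the sole primary outcome, does not depend on the exclusion rule. A reader might infer that the trial's main comparison is compromised, but the Protocol gives no support for that.

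*The authors surely meant endline pairs only.* This is likely, since receipt has no meaning before the programme, and a statistical analysis plan could add the phase limit. A reader might infer that the analysis cannot be run at all, but that holds only for the rule taken literally. The endline-only version can be fitted. It remains open to selection, so the clarification cures the empty cell and leaves the bias.

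*Coverage may be near complete.* Section 2.3.1 targets by age without a means test, section 3.2.2 enrols all eligible women and children in the selected villages, and Table 1 gives each sampled age at least 12 months of possible exposure. This stands as a limit on size, and it is why the 95% row matters. None of these passages reports coverage achieved.

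*The direction is unknown.* This stands. It is tempting to infer an upward bias, on the view that unpaid households are poorer and more remote. Section 2.3.1, however, describes inequality within the villages as negligible, and section 2.2 describes all of them as poor and remote. The inclusion of severely malnourished children under five could pull the other way.

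**Conclusion.** The point holds as a should-fix on a secondary analysis. The Protocol fixes a rule and a label that do not match: the result would not be a TOT effect. As written, the rule also leaves the planned model without a baseline intervention cell. Restricted to endline, it gives an interaction that combines programme effect and selection.

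The size rests entirely on assumed coverage and an assumed gap: about 0.005–0.025 z at 95% coverage with gaps of 0.1–0.5 z, and 0.02–0.08 z at 80–90% coverage with gaps of 0.2–0.4 z, set against 0.20. These are illustrations, and the sign is open. That selection enters the coefficient follows from the rule itself whenever some pairs are unpaid and they differ from those who are paid.

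**What to change.** 1. Delete the exclusion analysis, or keep it labelled as descriptive, restricted to endline and not called TOT.
2. Define TOT as an instrumental-variable estimate: regress the outcome on actual receipt (zero at baseline and in controls), with receipt instrumented by phase×group, phase and group in the model, and standard errors clustered by village. With unpaid controls and no covariates, this is the intention-to-treat estimate divided by the endline receipt rate.
3. For binary outcomes such as stunting, use a linear model on the risk-difference scale. The ratio does not carry over to the logistic models of section 3.2.6.
4. Record individual receipt at endline and say what counts as receipt. Sections 3.1 and 3.2.1 plan to study the use of funds, but section 3.2.5 lists no individual receipt item.
5. State the assumption that assignment affects outcomes only through receipt. Home visits and education sessions (sections 2.1 and 2.3.3), or spillover from paid neighbours, could reach unpaid mothers and violate it. If they help those mothers, the ratio overstates the effect of cash.

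The cost is a change of wording and one or two questionnaire items. The estimate will have a wider interval than the naive per-protocol one. Treating c as known, its standard error is that of intention-to-treat divided by c: 1/0.95 = 1.05 times as large at 95% coverage, 1/0.80 = 1.25 times at 80%. It also relies on the assumption in item 5.

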**Child’s anthropometrics**

- HAZ

Secondary outcomes:

- Stunting
- WHZ, wasting

Intermediate outcomes:

**Nutrition pathway**

- Child’s nutrition: IYCF practices (DDS7, MDD, MMF, MAD, iron-rich foods), consumption of animal source foods (ASF)
- Mother’s nutrition: MDD-W, DDS 10, number of meals, consumption of ASF
- Household food insecurity: HFIAS (HHS)
- Household food expenditures (as opposed to non-food expenditures)

**Health pathway**

- Child’s health: morbidity over the previous 15 days, child’s health since birth as perceived by the mother, vaccinations, vitamin A supplementation, deworming, regular medical follow-ups and age at last medical follow-up, health-seeking behavior (children taken to a health center if sick)
- Maternal health: antenatal and postnatal care (number of consultations, stage of pregnancy at first antenatal visit, malaria IPT, tetanus vaccines, iron supplementation) delivery in health facilities, delivery assisted by a skilled birth attendant, birth weight and LBW of newborns

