## **2.2. Intervention areas**

The CT project will be concentrated in the two northern regions (Kara and Savanes) and some of the villages under ICCM-Nut supervision. The ICCM-Nut is active in 365 villages in the Kara region and 200 in the Savanes region. These localities, called CTC (“Community Therapeutic Care”) villages, were identified by UNICEF based on their isolation and distance from the closest peripheral care unit (UPS). Because the available financial resources will not allow for all CTC villages to be covered, the following refined targeting process will be used:

-Choosing the poorest districts, with the most concerning nutritional indicators, in both regions. The chosen districts are as follows: (a) Kpendjal and Oti from the Savanes region, and (b) Dankpen, Doufelgou, and Kéran from the Kara region.

-Using random selection to identify the villages to be covered within these districts.

The localities chosen for the pilot phase are very poor, remote villages, with little to no access to basic social services (for example, the closest healthcare unit is typically at least five kilometers away).

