### **2.3.3. Conditionalities**

The selected conditionalities will be flexible and non-exclusive, and should help communities adopt behaviors conducive to the well-being and welfare of children. Mothers who meet these conditionalities will receive a small bonus at the end of the program. The conditionalities for each child are as follows:

- Possession of a birth certificate or an attestation to the ongoing procuration of a civil

status document

- Mother/guardian’s attendance at educational meetings concerning childhood needs

- Mother/guardian’s regular attendance at monthly childhood growth-tracking meetings

- At least four antenatal consultations (for pregnant mothers)

- Keeping children under 15 years old living at home (as opposed to in foster care)

- Primary school attendance for all children of age in the household, in order to avoid

child trafficking and exploitation

Community agents in charge of the project’s implementation will provide each household with the necessary accompaniment (information, referrals, administrative procedures, etc.) for the purpose of promoting the adoption of these proposed conditionalities.

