**Mother’s characteristics:** This component consists of mothers’ civil statuses, education levels, and revenue sources.

**Schedule and child care:** Mothers’ schedules will be examined, as they can directly influence dietary practices and child care. The time mothers spend taking care of their children (meals, games, healthcare) will be observed with particular interest.

**Mother’s status, autonomy, and decision-making power:** This component will assess women’s household autonomy (particularly with regard to finances), the treatment they endure within the household (abuse, insults, anxieties, etc.), their involvement in sensitization meetings and social/community networks, and their decision-making power relative to issues of diet, health, education, family planning, and children’s rights within their households.

**Use of health services and attendance at informational sessions:** This component will take into account pregnancy history, household situations during the course of pregnancy (reduced work, improved diet, etc.), the number of pre- and post-natal consultations, birth setting and external help received, and mothers’ involvement in training sessions on children’s health, diet, and rights.

**Mother’s knowledge, attitudes, and practices (“CAP”):** The program aims to improve mothers’ knowledge bases in order to impact their dietary practices and their conduct relating to the caretaking, hygiene, nutrition, and rights of their children. After adjusting for certain variables such as education and socioeconomic levels, changes in the CAP between the baseline and endline surveys will be examined to evaluate the program’s impact pathways. The CAP questionnaires will be adapted to the content of the monthly information sessions planned in the project.

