**DIetary diversity:** A dietary diversity score will be calculated for each mother following a qualitative recall of items consumed over the previous 24 hours. These scores will be determined by tallying the number of food groups consumed out of 12 total food group classifications. However, as there are currently no international recommendations for an optimal number of food groups or a “good dietary diversity” threshold for women of childbearing age, information will be collected from a larger number of groups and subgroups; thus, indicators can be constructed *a posteriori* according to recommendations adopted in the future (which should soon be implemented on an international level, hence during program implementation).

**Anthropometry:** Mothers’ height and weight will be measured in accordance with WHO recommendations. Along with body mass index, this raw data can be used to evaluate mothers’ nutritional statuses, which are known as a major factor in newborns’ nutritional statuses at delivery.

❖ **PERTAINING TO CHILDREN**

**Child’s health:** This component will gather information regarding possession of health records, children’s immunizations, growth charts, and children’s morbidity over the previous 15 days. Additionally, in cases of illness, mothers’ appetites and responses to said illnesses will be assessed during consultations at a health center (or elsewhere).

**Dietary practices:** Standard dietary practices indices for infants and young children, as recommended by the WHO, will be calculated following a qualitative recall of children’s feeding practices over the last 24 hours—for example, dietary diversity (number of food groups consumed out of seven total), frequency of ingestion (total number of meals and snacks consumed), consumption of foods of animal origin, consumption of iron-rich products, etc. Retrospective questions about breastfeeding will also be asked (initiation and cessation, exclusive breastfeeding), as well as questions about the introduction of complementary feeding and how the mother feeds her child (preparation of specially adapted meals, help with eating, encouraging consumption).

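### Birth weight and LBW are known only for babies weighed at birth; if the programme changes who is weighed, their difference-in-differences estimate is biased in an unknown direction

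*Protocol*

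**What the plan says.** Section 3.2.1 of the protocol plans that "cross-sectional surveys of children aged six to 29 months and their mothers will be conducted in these villages". Section 3.2.2 gives other upper age limits for the two surveys but the same lower limit of six months. No section provides for weighing newborns. Section 3.2.5 covers items that bear on whether a birth weight exists. For the child: "This component will gather information regarding possession of health records". For the mother, the items on pregnancy and delivery include "birth setting and external help received".

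The health pathway in section 3.2.6 pre-specifies "delivery in health facilities, delivery assisted by a skilled birth attendant, birth weight and LBW of newborns" with no restriction on which newborns count. The same section applies one difference-in-differences model to all indicators and treats the interaction coefficient as impact attributable to the transfers or their conditionalities. It explains the coefficients this way: "Using birthweight as an example, the table and figure below illustrate the significance of the various coefficients described above".

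On access to care, section 2.2 says of the pilot villages that "the closest healthcare unit is typically at least five kilometers away". On what the programme does, section 2.3.1 enrols women during pregnancy, and section 2.3.3 lists this conditionality: "At least four antenatal consultations (for pregnant mothers". Mothers who meet the conditionalities receive a small bonus. Section 3.2.1 names use of health services among the ways the programme may work.

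**The concern.** Randomisation and intention-to-treat analysis protect a comparison of all surveyed children. They do not protect a comparison restricted to children with a known birth weight, because membership of that group is settled after randomisation by an event the programme is meant to influence. Facility delivery and skilled attendance, the likeliest occasions for weighing, stand in the same list item as birth weight.

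Differencing against baseline does not help. It removes differences between arms that were already there and changes common to both. A change in who is weighed that is caused by the programme arises only in the intervention arm, after baseline. It breaks the equal-evolution assumption on which section 3.2.6 relies.

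A programme that succeeded in bringing more births into care could then appear to lower birth weight, if the added births are lighter, or to raise it, if they are heavier. A real gain could also be hidden.

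**Working it through.** **The plan's own figure.** There is none to reproduce. The protocol gives no share weighed, no birth-weight mean or SD, and no sample size for these outcomes. The calculation in section 3.2.3 concerns HAZ and stunting only.

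**Set-up, with a true effect of zero.** Let c be the share of births with a known weight without the programme (control arm, and both arms at baseline) and t > c the share in the intervention arm at endline. Assume births weighed without the programme would also be weighed with it. Let d be the mean of the newly weighed births minus the mean of the others. The weighed mean in the intervention arm at endline is

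[c·μ + (t − c)(μ + d)] / t = μ + d(t − c)/t.

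The other three cells have mean μ, so the bias in the difference-in-differences is d(t − c)/t. It takes the sign of d, and it is zero if d = 0 or t = c. For LBW, d is the difference in LBW proportion.

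**Illustration (all inputs assumed).** c = 0.45, t = 0.65; 3,000 g and 10% LBW among births weighed anyway; 2,850 g and 20% LBW among the newly weighed.

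- Mean: (0.45 × 3,000 + 0.20 × 2,850)/0.65 = 2,954 g, a spurious −46 g. Check: −150 × 0.20/0.65 = −46.2.
- LBW: (0.45 × 10 + 0.20 × 20)/0.65 = 13.1%, a spurious +3.1 points.

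**Range.** Assumed: mean 3,000 g, SD 450 g, normal distribution, ICC 0.05, and 1,020 less 10% = 918 children per arm in each survey over 81 villages (1,020, 10% and 81 are from section 3.2.3; the same number is assumed at endline). Each cell has N = 918 × share weighed and variance 450² × [1 + (N/81 − 1) × 0.05]/N; the four variances are summed. False positives are at a two-sided 5% level.

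| c → t | bias at d = ∓200 g | LBW shift, d = −200 / +200 | SE | false-positive rate |
|---|---|---|---|---|
| 0.40 → 0.50 | ∓40 g | +2.4 / −1.5 points | 49.9 g | 12.6% |
| 0.50 → 0.65 | ∓46 g | +2.8 / −1.7 points | 45.6 g | 17.3% |
| 0.60 → 0.80 | ∓50 g | +3.0 / −1.8 points | 42.5 g | 21.7% |
| 0.70 → 0.80 | ∓25 g | +1.5 / −0.9 points | 40.7 g | 9.4% |

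With d = ±100 g the bias halves; in the last row it is 12.5 g and the rate is 6.1%. With d = 0 the rate is 5%.

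**The case against.** **Handling of missing birth weights normally belongs in the SAP, which is not at hand.** That is fair, and the absence of such detail is not the point. The protocol itself fixes the outcome, the estimator and the causal reading, and for this outcome the three do not fit together.

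**The documents do not show that the programme changes who is weighed.** This stands. A reader might infer that the birth-weight contrast is certainly biased; the text does not support that. Antenatal visits are a conditionality, but a flexible one, and facility delivery is only an outcome to be tested. The distance to care applies to both arms, and control villages also receive UNICEF activities. By Table 1, children aged 24 to 29 months at endline were first exposed at birth or later, so their weighing at birth could not have been changed by the programme, which limits t − c.

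**The worked example proves nothing.** Also correct. It explains coefficients, and its table and figure are not shown. It cannot be read as a claim that weighed babies are comparable between arms.

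**The size is assumed and modest.** True. In the 45% versus 65% case the standard error is 450 × √[3/(918 × 0.45) + 1/(918 × 0.65)] ≈ 43 g before clustering, so the 46 g bias is about one standard error. That raises the false-positive rate without making a false finding likely.

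**Health-seeking.** The outcome "health-seeking behavior (children taken to a health center if sick" also conditions on something the programme may change, because 15-day morbidity is in the same list. It is tempting to redefine it over all children. That would be no better: the redefined proportion falls when illness falls, so a health gain would look like worse care-seeking.

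**Conclusion.** The point holds in conditional form. Birth weight and LBW are analysed in a subset formed after randomisation, and the protocol draws an impact conclusion from it without qualification. Bias follows if two things are both true: the programme raises the weighed share in the intervention arm, and the newly weighed births differ from the rest. Neither is established, and the sign cannot be known in advance. Across the assumed scenarios the bias is about 12 to 50 g in either direction, LBW shifts by between −1.8 and +3.0 points, and the nominal 5% error becomes about 6% to 22%.

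The reach is limited. These are two of many intermediate outcomes. HAZ, stunting, WHZ and wasting come from the survey's own measurements and are not touched. The change is worth making because it is cheap and prevents a possible false conclusion, not because the trial's main result is at risk.

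**What to change.** In section 3.2.6:

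1. State the source of birth weight (record, recall, or both).
2. Report whether a birth weight was recorded as an outcome in its own right, by arm and survey, over all surveyed children.
3. Accompany the birth-weight and LBW estimates with bounds for the extra weighed births, or with inverse-probability-of-being-weighed weights built from covariates already collected. Trimming bounds need the assumption that no birth loses its weighing because of the programme; weights need the covariates to explain who is weighed.
4. Do not read the estimate as programme impact if the weighed share differs between arms and the bounds include zero.
5. Keep health-seeking among sick children as defined, and read it beside 15-day morbidity by arm.

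The mother's perception of size at birth may be added for all births if it is not already asked, but only as supportive evidence: it is subjective and respondents know their arm.

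The cost is a few lines of analysis text and a less precise birth-weight estimate, with no extra participants. The loss of precision can be large. In the 45% versus 65% illustration, trimming removes 0.20/0.65 = 31% of the weighed intervention births. With a normal distribution and SD 450 g, that moves the mean by 450 × 0.352/0.692 ≈ 229 g each way (0.352 is the normal density at the trimming point, 0.692 the share kept). Bounds that wide would usually include zero, and reporting them says plainly what the data can support.
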